# Stop Antibiotics on guidance of Procalcitonin Study (SAPS): a randomised prospective multicenter investigator-initiated trial to analyse whether daily measurements of procalcitonin versus a standard-of-care approach can safely shorten antibiotic duration in intensive care unit patients - calculated sample size: 1816 patients

**DOI:** 10.1186/1471-2334-13-178

**Published:** 2013-04-16

**Keywords:** Antibiotics, Antibiotic duration, Biomarker, Critical illness, C-reactive protein, Defined daily dosage, Intensive care unit, Procalcitonin, Sepsis, Septic shock

## Abstract

**Background:**

Unnecessary long-term use of broad-spectrum antibiotics is linked to the emergence and selection of resistant bacteria, prolonged hospitalisation and increased costs. Several clinical trials indicate that the biomarker procalcitonin (PCT) can guide antibiotic therapy. Some of these trials have shown a promising reduction in the number of antibiotic prescriptions, duration of antibiotic therapy and even length of stay in the ICU, although their size and selection criteria limit their external validity. The objectives of the Stop Antibiotics on guidance of Procalcitonin Study (SAPS) are to evaluate whether daily PCT can improve “real-life” antibiotic use in Dutch ICU’s by reduction of the duration of antibiotic treatment without an increase of recurrent infections and mortality.

**Methods/Design:**

Multicenter randomised controlled intervention trial. Powered for superiority of the primary efficacy endpoint and non-inferiority on the primary safety endpoints (non-inferiority margin is set on 8%).

Inclusion criteria: (1) ICU-patients aged ≥18 years and (2) receiving antibiotics for a presumed or proven infection and (3) signed informed consent. Exclusion criteria: (1) patients who require prolonged antibiotic therapy, (2) suffer from Mycobacterium tuberculosis, (3) cystic fibrosis, (4) viral or parasitic infections and (5) those that are severely immunocompromised or (6) moribund.

The intervention consists solely of an advice to discontinue antibiotic treatment in case PCT has decreased by more than 80% of its peak level (relative stopping threshold) or decrease below a value of 0.5 ng/ml (absolute stopping threshold).

The study hypothesis is that PCT-guided therapy is non-inferior to standard care based on implemented guidelines and local expertise, whilst reducing antibiotic usage. Computerised 1:1 randomisation will allocate 908 patients per arm. Arm 1: standard of care. Arm 2: procalcitonin-guided therapy. The primary efficacy endpoint is consumption of antibiotics expressed as the defined daily dosage and duration of antibiotic therapy expressed in days of therapy. This trial is designed to shorten antibiotics safely, therefore the primary safety endpoint is mortality measured at 28 day and 1 year.

**Discussion:**

This will be the largest procalcitonin-guided antibiotic intervention trial in ICU setting thus far. Currently 1600 of the planned 1816 patients are randomised (November 2012). The first interim analysis has passed without any safety or futility issues.

**Trial registration:**

Trial registration number at http://www.clinicaltrials.gov: Id. Nr. NCT01139489
, at http://www.trialregister.nl: Id.nr. NTR1861.

## Background

Resistance to antimicrobial drugs is an increasing threat to public health. Each year, about 25.000 people die in the EU from an infection with multidrug-resistant bacteria. In the EU infections due to such bacteria result in extra healthcare costs of over 1.5 billion Euros each year [1]. The reasons for the increase in antimicrobial resistance are complex, but it has become evident that unnecessary prolonged use of broad-spectrum antibiotics is linked to the emergence and selection of resistant bacteria, and longer hospitalization [1]. The Netherlands have long been known for its prudent use of antibiotics and its subsequent low number of multi-resistant organisms. However, in the Netherlands in recent years a gradual increase in multi-resistant organisms has been found, mainly located in nursing homes and intensive care units (ICU’s).

In general, the use of different classes of antibiotics has grown steadily in hospitals [2]. In 2000, a survey in Dutch hospitals showed that the overall use of systemic antibiotics was 43 Defined Daily Dose (DDD)/100 patient-days. In 2009 the use of systemic antibiotics had already increased to 70.9 DDD/100 patient-days [3]. In the ICU’s of these hospitals the average use was twice as high (132 DDD/100 patient-days in 2006) [4].

Delayed antibiotic therapy is associated with a worse outcome for patients presenting with a severe acute infection. Each hour of delay in the administration of antibiotic therapy in the first six hours is associated with an average decrease in survival of more than 7% [5]. It is therefore advised to start antibiotics as soon as possible whenever sepsis is considered. Although rapid and adequate antibiotic therapy is of great importance, it is obvious that aggressive strategies can easily lead to a high consumption of broad-spectrum antimicrobial agents. Unfortunately, no objective measures exists on how long antibiotic therapy should be applied. To address the potential overuse of antimicrobial agents, trials have used biomarkers to provide additional objective information about the extent of systemic inflammation and to optimise the duration of antibiotic therapy. Conventional clinical signs such as fever, leukocytosis or increased C-reactive protein (CRP), have proven to be neither specific nor sensitive enough for the diagnosis or treatment of infections in ICU patients.

Over the past two decades procalcitonin (PCT) has been extensively studied as a serum marker of systemic infection and sepsis. Being the precursor of the active hormone calcitonin, PCT is a 116 amino-acid peptide that can be elevated by several orders of magnitude in systemic inflammation accompanying sepsis [6,7]. It has been shown that after trauma or surgery the levels of PCT usually stay below 1 ng/ml [8]. On the other hand, PCT levels that are clearly above 1 ng/ml are often associated with severe bacterial infections that manifest themselves as sepsis and septic shock [6-10].

Previous studies have shown that PCT-guided therapy is not only beneficial for respiratory tract infections [11-14], but also provide useful guidance for antimicrobial treatment in critically ill patients in the ICU who are treated for suspected bacterial infection [15-19]. The large French multicenter PRORATA study demonstrated that patients in the PCT group had significantly more antibiotic free days than patients in the control (usual care) group (14.3 days [SD 9.1] vs. 11.6 days [SD 8.2])[17]. Mortality in the PCT group was non-inferior to that in the control group. Criticism focused on potential treatment bias, unclear adherence to guidelines in the control group, the sample size (630 randomized patients may be underpowered), and especially the 10% non-inferiority margin. The 10% inferiority margin ought to have been a relative measure. However, the PRORATA-study was powered upon a 10% absolute difference in mortality. Such a difference is generally considered unacceptable. Therefore, safety issues remain and it is also not clear whether such a PCT-guided strategy is effective in a setting with relatively low antibiotic consumption and low resistance such as the Netherlands. PCT-guided antibiotic therapy might be beneficial to patients but also to the society at large, because it may lead to lower costs, fewer side effects originating from antibiotic usage and, in time, potentially a decrease in multidrug-resistance. Thus, we designed a large multicenter Dutch PCT-guidance trial to address all of these issues, in particular the optimisation of antibiotic therapy duration in critically ill patients on the ICU, currently solely based on empirical guidelines.

## Methods and design

### Study aim

The objective of this trial is to establish whether the PCT-guided strategy is superior to standard of care based on existing experience, expertise and implemented guidelines. The primary efficacy endpoint is that PCT-guided strategy is superior in terms of antibiotic use, expressed as the Defined Daily Dosage (DDD), and duration of antibiotic therapy expressed in days of therapy. As this trial is designed to shorten antibiotics safely, the primary safety endpoint will be overall mortality measured at 28 days and at 1 year.

Secondary endpoints are reinfection rate, length of stay in the ICU and cost effectiveness.

### Study design and setting

This is a nationwide multicenter prospective, randomised, controlled, open intervention trial performed in 16 Dutch surgical and medical ICU’s.

The Ethics Committee of the VU University Medical Center Amsterdam, Netherlands, approved the study protocol which is in full compliance with the Helsinki declaration. The study is coordinated by a steering committee (the authors), consisting of intensivists from participating ICU’s, who all contributed to the design and execution of this trial. Furthermore, a statistician, an epidemiologist and a pharmacist support the steering committee.

The trial is supervised by an independent safety monitoring board that is not involved in the design and conduct of the trial, or in the recruitment of patients. The board consists of a pulmonologist, an intensivist and a statistician.

### Stratification, randomisation and blinding

Patients will be stratified by diagnosis and centre. Stratification will be performed according to the diagnosis of sepsis, severe sepsis and septic shock. Allocation of patients to either treatment group is concealed by using a centralised randomisation procedure with a computer generated list produced by an independent research organisation, the Julius Center for Human Research, Utrecht, the Netherlands.

### Patients

Included will be patients with an age >18 years, and for whom antibiotics were initiated for an assumed or proven infection on admission or during ICU admission. Current guidelines, like the Surviving Sepsis guidelines, advocate swift initiation of antibiotics whenever infection/sepsis is considered [5]. This study will not interfere with this decision of the physician to start antibiotics. The study, therefore, is the ultimate combination of early-goal-directed therapy and reduction of antibiotic duration. Patients can be included within 24 hours after receiving their first dose of antibiotics. Informed consent has to be obtained in writing from the patient or his or her legal representatives prior to inclusion.

Exclusion criteria are: (1) the inability to acquire a written informed consent, or (2) when prolonged antibiotic therapy is indicated (>3 weeks, e.g. endocarditis, cerebral/hepatic abscess), (3) patients with severe infections due to viruses, parasites or tuberculosis, (4) patients entering the ICU for merely short-term post-operative observation, (5) patients with an estimated length of stay less than 24 hrs, (6) patients suffering from cystic fibrosis, (7) severely immunocompromised patients such as patients with HIV and a CD4 count of less than 200 cells/mm, neutropenic patients (<500 neutrophils/mL), (8) patients with solid organ transplantation, or (9) moribund patients.

The use of corticosteroids does not interfere with PCT measurements, while effects on CRP levels have been demonstrated [20]. Since the purpose of this study is to demonstrate the efficacy and safety of PCT-guided therapy in a real-life setting patients on corticosteroid therapy will not be excluded from the study. Use of systemic corticosteroids will be monitored and recorded throughout the trial.

### Treatment and intervention

The decision to start antibiotic treatment will in no way be affected by the trial. In all patients antibiotics will be started based on a clinical suspicion of infection or microbiological evidence of infection. This decision is fully at the discretion of the treating intensivist. Once antibiotics are administered for newly suspected or proven bacterial infection, patients or their legal representatives will be asked for informed consent. If informed consent is obtained, the patient will be randomised to either the standard therapy arm (control group) or the PCT arm (intervention group). Randomisation will be stratified for diagnostic group and study centre. When a patient is randomised for the control group, no PCT measurements will be performed. Other laboratory tests for infection such as CRP are allowed. When a patient is randomised for the PCT group, PCT will be measured at base-line called the T0-serum sample (T0: as close to initiation of antibiotics as possible, at least within 24 hrs). On the following days the ICU team will be provided with daily PCT values until ICU-discharge or until the third day after all systemic antibiotics have been discontinued. Along with daily PCT values a non-binding advice will be generated to consider stopping the prescribed antibiotics if PCT has decreased to <20% of its peak value (relative stopping threshold) or has reached a value of below 0.5 ng/ml (absolute stopping threshold). PCT levels will not be used to initiate antibiotic therapy. In case of two consecutive PCT levels below 0.5 ng/ml a stopping advice will be generated.

As for the control group, the physician will receive routine daily laboratory values as requested and no additional advice. Thus, treatment for both patient groups will be based on existing experience, expertise and local protocols, however, in the intervention group doctors are additionally provided with daily PCT levels, and a non-binding advice on continuation or discontinuation of antibiotic therapy by email, electronic patient data management system feedback, or research nurses. In both groups daily multidisciplinary reviewing will be performed on antibiotic therapy and duration, based on the clinical course, microbiological results and treatment guidelines. If doctors do not adhere to the stopping rules, reasons for non-adherence will be recorded.

### Data collection and management

Data management will be performed by the investigators or research nurses of the participating ICU. The investigators must ensure that the patient’s anonymity is maintained. The subjects will be identified by a trial identification number. The list containing the subjects name and allocation numbers are kept in strict confidence by the principal investigator. The database used for electronic data transfer of any clinical research file (CRF) or subject related data will be protected by a password. Data base integrity and data safety as well as privacy are warranted by the contracted research organisation, the Julius Center for Human Research, Utrecht, the Netherlands.

### Procalcitonin assays

PCT will be measured with various validated assays: the automated Kryptor platform (Thermo Fisher Scientific, Hennigsdorf, Germany), the Roche Elecsys Thermo Fisher Scientific PCT assay, the Siemens Centaur Thermo Fisher Scientific PCT assay or using BioMerieux’s Vidas Thermo Fisher Scientific PCT assay. The Thermo Fisher Scientific Kryptor sensitive PCT will be applied on this platform using Time Resolved Amplified Cryptate Emission (TRACE) technology and is based on a polyclonal antibody against calcitonin and a monoclonal antibody against katacalcin, which binds to the calcitonin and katacalcin sequence of the calcitonin pro-hormone. The test is considered a homogeneous immunoassay (sandwich principle) and is validated on serum and plasma (EDTA and heparin) matrix. The direct measuring range of the assay is from 0.02-50 ng/ml, with automated dilution extending the upper range to 1000 ng/ml. The Functional Assay Sensitivity (FAS) is 0.06 ng/ml.

The Roche Elecsys Thermo Fisher Scientific PCT assay also uses an immunoassay based on a sandwich principle based on a polyclonal antibody against calcitonin and a monoclonal antibody against katacalcin, which binds to the calcitonin and katacalcin sequence of the calcitonin prohormone. The direct measuring range of the assay is from 0.02-100 ng/ml. The Functional Assay Sensitivity (FAS) is 0.06 ng/ml. Procedure time of the assay is 18 minutes. The assay is validated on serum and plasma (EDTA and heparin) matrix.

The BioMerieux Vidas Thermo Fisher Scientific PCT assay is an Enzyme-Linked Fluorescent Assay (ELFA) involving a one-step immunoassay sandwich method using a Solid Phase Receptacle (SPR). The system uses a ready to use test strip into which a sample volume of 200 micro litres of serum or lithium heparin plasma is pipetted. The direct measuring range is 0.05-200 ng/ml. The FAS is determined to be 0.09 ng/ml.

Procedure time for all these assays is less than 30 minutes. Each participating centre will have access to a Kryptor machine, a suitable Vidas or Roche immunoanalyser to expedite the determinations and its adjunctive advice.

Whenever results exceed the maximum measuring range of any of the above described machines, manual dilution will be used, in accordance with the manufacturer’s specifications to achieve the true quantified value of a patient result. All patient results will be given in two decimals for the entire measuring range.

### Sample size and statistical analysis

Antibiotic duration is the main primary outcome of this on-going study. The expected standard deviation (SD) of antibiotic treatment, based on previous intervention trials [15-20] will be 6 days in both groups. Assuming a mean baseline antibiotic duration of 8 days, with a significance α-level of 5% and a power of 90%, 757 patients are needed in both groups. Patients that are discharged from the ICU before a stopping advice could have been issued and who are still being treated with antibiotics are considered “dropped out”. Assuming a drop-out rate of 20%, we need to include 908 patients in each group, so for the superiority margin in total 1816 patients will need to be included.

As the PCT intervention arm should be non-inferior, in terms of safety (mortality), in comparison to the standard treatment, the non-inferiority margin for PCT guided antibiotic management regarding 28-day-mortality is set on 8%. Based on previous trials, like the PRORATA-study [17], we assumed a 28% mortality rate in each group. With a one-sided significance α-level of 2.5% and a power of 90%, 714 patients are needed in both groups. Again with a drop-out of 20%, 1714 patients will need to be included. With such a sample size (and alpha 5% and beta of 20%) we would have been able to detect a 15% relative increase in mortality. Such conventional boundaries are very acceptable in most trials investigating the efficacy of new drugs. Here, we aim to do better, with an alpha of 2.5% and beta of 10%.

Losses to follow-up on both arms will be registered including the reason for loss to follow-up. Furthermore, the primary endpoint will be explored for association with potential prognostic factors in a survival analysis. The factors that will be considered are age, sex, APACHE IV-score, SOFA-score and usage of corticosteroids or dialysis.

The primary analysis population will consist of all randomized patients following the intention-to-treat principle. For the primary analysis, losses to follow-up (in both arms) will be included in the 28-day analysis of mortality and antibiotic consumption. The primary analysis will be repeated with the subset of patients who complied with the stopping threshold, as so-called “per protocol analysis” of mortality and antibiotic consumption on day 28.

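### The 20% 'drop-out' allowance covers patients who stay in the intention-to-treat analysis with little or no effect, so it does not preserve the stated 90% power for antibiotic duration

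*Protocol article*

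**What the plan says.** All statements are in the protocol article.

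- Sample size and statistical analysis: "Antibiotic duration is the main primary outcome of this on-going study". The standard deviation "will be 6 days in both groups". The baseline mean is 8 days, alpha 5% (sidedness not given) and power 90%, from which "757 patients are needed in both groups". The difference to be detected is not printed.
- Same section: the drop-outs are defined as "Patients that are discharged from the ICU before a stopping advice could have been issued and who are still being treated with antibiotics". They are assumed to be 20%, which takes the number to 908 per arm, 1816 in total.
- Same section, on the analysis: "The primary analysis population will consist of all randomized patients following the intention-to-treat principle". Losses to follow-up in both arms are also kept in the 28-day analysis of mortality and antibiotic consumption.
- Treatment and intervention: "the ICU team will be provided with daily PCT values until ICU-discharge", or until the third day after all systemic antibiotics have stopped. The abstract describes the intervention as nothing more than the advice to stop.

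**The concern.** A drop-out allowance replaces patients who will contribute no data. The patients defined here do contribute data: they are alive at ICU discharge, on a known antibiotic course, and their days of therapy can be counted. What they lack is the intervention. By definition no stopping advice could be issued before discharge, and the daily values end at discharge, so none follows. Under intention-to-treat they enter both arms with an expected difference at or near zero and pull the overall mean difference towards zero.

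Lost numbers and a diluted effect have different costs. Losing a fraction d of patients requires n/(1 − d). Diluting the effect by a fraction d requires n/(1 − d)², because n varies with the inverse square of the difference. The plan makes an allowance of the first kind for a problem of the second kind. At stake is whether the 90% power claimed for the main primary outcome belongs to the analysis that is planned.

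**Working it through.** **Inputs.** SD 6 days, alpha 5%, power 90%, 757 per arm before and 908 per arm after a 20% allowance (all from Sample size and statistical analysis). Assumed, because not printed: two-sided alpha; a difference of 1.0 day; an unchanged SD of 6 in the mixed population.

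**Step 1: reproduce the plan's figures.** n per arm = 2 × (1.960 + 1.2816)² × SD² / difference².

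- With SD 6 and a difference of 1 day: 2 × (3.2416)² × 36 / 1 = 756.5, rounded up to 757. This matches.
- Solving in reverse from 757: 6 × 3.2416 × √(2/757) = 1.00 day.
- 757 × 1.2 = 908.4, which the article gives as 908.

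**Step 2: dilution.** Let f be the share of the full 1-day effect kept by the 20% discharged before advice. The intention-to-treat difference is 0.8 × 1 + 0.2 × f. The standard error with 908 per arm is 6 × √(2/908) = 0.2816. Power = Φ(difference/0.2816 − 1.960).

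| Effect kept by the 20% (f) | ITT difference (days) | Power, 908 per arm |
|---|---|---|
| 0 | 0.80 | 81.1% |
| 25% | 0.85 | 85.5% |
| 50% | 0.90 | 89.2% |
| 75% | 0.95 | 92.1% |
| 100% (1 day already applies to all randomised) | 1.00 | 94.4% |

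For the zero-effect row: 0.80/0.2816 = 2.841, and Φ(2.841 − 1.960) = 0.811.

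**Step 3: break-even.** 90% power with 908 per arm needs a difference of 3.2416 × 0.2816 = 0.913 day. Setting 0.8 + 0.2f = 0.913 gives f = 0.56. The early-discharged patients would have to keep more than half of the full effect without any stopping advice.

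**Step 4: size of the gap.** For 90% power at 0.8 day, n = 756.5/0.64 = 1,182.1, so 1,183 per arm against 908 planned.

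**Step 5: sensitivity.**

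- *Sidedness.* If 5% is one-sided, 757 back-solves to 0.90 day, which dilutes to 0.72 day; power is about 82%.
- *Share of early discharges, zero effect in them.* A 10% share gives a 0.90-day difference and 89%; a 25% share gives 0.75 day, 0.75/0.2816 = 2.663, and Φ(0.703) = 76%.
- *Reference case.* If the 20% really left the analysis, 908 × 0.8 = 726 per arm would remain and power for 1 day would be 88.8%. That small shortfall arises because the allowance multiplies by 1.2 rather than dividing by 0.8 (757/0.8 = 947), which is a separate matter.

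**The case against.** The strongest reply is that the 81% is conditional. The article prints neither the 1-day difference nor the population it refers to. If 1 day was meant as the difference over all randomised patients, taking 80% of it discounts the same thing twice, and power is 94%. This stands as a possible reading and belongs in the range. It sits badly with the text, though: on that reading these patients are already allowed for in the target, and the 20% allowance has no purpose.

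Second, zero effect is the least favourable case. The ICU team sees daily values as well as the advice, so some influence before discharge is conceivable. This also stands, and is why results are shown for partial effects. Zero remains the natural reading of a group defined by the absence of any possible advice.

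Third, even the zero-effect figure is just above 80%, and dilution does not inflate the type I error of the superiority test. That is correct and limits the severity.

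Two stronger readings are tempting but unsupported. A reader might infer from the drop-out label that these patients will be removed, so that randomisation is broken on the primary endpoint. The article plans no such exclusion: the label occurs only in the sample size calculation, and the analysis text keeps all randomised patients. A reader might also recompute power at the level of 0.0294 and report a lower figure still. The Interim analysis section gives that level for the interim, alongside the 8% mortality margin, and does not say that it governs the final test of antibiotic duration.

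**Conclusion.** The concern holds as an inconsistency between the sample size and the planned analysis. One fifth of patients are costed as lost numbers but analysed as patients with little or no intervention effect. On the natural reading, the intention-to-treat comparison of antibiotic duration has about 81% power, not 90%. This rests on the back-solved 1-day target applying to patients who can receive advice, zero effect in the 20%, and an SD that stays at 6. Power reaches 85.5% or 89.2% if a quarter or half of the effect persists, and 94% only under the all-randomised reading of the target.

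The primary test remains valid and the trial is not undermined; the power statement is what is wrong. It should be corrected, but it is not a fatal defect. The figures concern the superiority endpoint only and say nothing about the power of the mortality comparison.

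**What to change.** 1. State the target difference in days, the sidedness of the 5%, and whether the target applies to all randomised patients or to those who can receive advice.
2. State that patients discharged from the ICU before any advice remain in the intention-to-treat analysis in both arms, with antibiotic days counted to day 28, including days after ICU discharge.
3. Stop using this group as a reason to inflate the sample size; keep any allowance for drop-out to patients whose outcome is truly missing.
4. Restate power for the intention-to-treat analysis with 908 per arm as about 81% under zero effect in the 20%, and show the range: 85.5% and 89.2% for partial effects, 94% if 1 day is an all-randomised target.

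The cost is a change of wording and a less favourable power figure. If antibiotic days after ICU discharge are not already recorded to day 28, they would have to be completed; the article does not say either way, although its 28-day consumption analysis implies that they are. No extra patients are needed.

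### The 20% drop-out allowance is applied as a factor of 1.2 instead of a division by 0.8, so 908 per arm leaves 726 patients, not the 757 stated as needed

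*Protocol article*

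**What the plan says.** All the figures are in the protocol article, section Sample size and statistical analysis.

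- **Efficacy (antibiotic duration).** The SD "will be 6 days in both groups", the control mean is 8 days, and "with a significance α-level of 5% and a power of 90%, 757 patients are needed in both groups". The difference to be detected and the sidedness of the 5% level are not given.
- **Drop-out.** A drop-out is a patient who leaves the ICU still on antibiotics before a stopping advice could have been given. The plan then says: "Assuming a drop-out rate of 20%, we need to include 908 patients in each group", and so "for the superiority margin in total 1816 patients will need to be included". The Abstract repeats the figure: "Computerised 1:1 randomisation will allocate 908 patients per arm".
- **Mortality (non-inferiority).** The base is 714 per group. The text continues: "Again with a drop-out of 20%, 1714 patients will need to be included".
- **Analysis population.** The primary analysis is by intention to treat in all randomised patients.

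No other drop-out rate or inflation rule appears in the article.

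**The concern.** A drop-out rate is a proportion of the patients enrolled. To end with n patients after a fraction d is lost, one enrols n/(1 − d). Multiplying by (1 + d) falls short, because the loss applies to the larger enrolled number. Both totals in the plan appear to come from the second rule.

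At stake is whether the stated sample size has its stated property. The article presents 90% power under 20% drop-out as a design feature, and it criticises an earlier trial for lack of power. If the inflation step is wrong, the enrolled number does not deliver the number that the same paragraph says is needed.

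**Working it through.** **Inputs from the plan:** 757 and 714 per arm before drop-out; 20% drop-out; 908 per arm (1,816) and 1,714 after drop-out; SD 6 days; alpha 5%; power 90%.

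**Assumptions:** a difference of 1 day and a two-sided test. Neither is stated. They are back-solved from 757 and are needed only for the power figures (steps 4 and 5).

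**1. Reproduce the base number.** n = 2 × SD² × (1.960 + 1.282)² / δ² = 2 × 36 × 10.507 / 1² = 756.5, so 757 per arm. This matches the plan. A one-sided 5% test with the same 1-day difference would give 617.

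**2. Reproduce the inflation.**

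| | Base per arm | × 1.2 | ÷ 0.8 | Plan states |
|---|---|---|---|---|
| Duration | 757 | 908.4 (908; total 1,816) | 946.25 (947; total 1,894) | 908; total 1,816 |
| Mortality | 714 | 856.8 (857; total 1,714) | 892.5 (893; total 1,786) | total 1,714 |

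Both stated totals match the × 1.2 column and neither matches the ÷ 0.8 column. Rounding does not explain a gap of 947 − 908 = 39 per arm, or 78 in total (78/1,894 = 4.1%).

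**3. What 908 per arm provides.**
- After 20% drop-out: 908 × 0.8 = 726.4, so 726. Shortfall: 757 − 726 = 31 (4.1%).
- Drop-out that still leaves 757: 1 − 757/908 = 16.6%.

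Steps 2 and 3 use only the plan's own numbers. They do not depend on the effect size, the sidedness or the test.

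**4. Power on the plan's own drop-out allowance.** Power = Φ(δ / (SD × √(2/n)) − 1.960).
- n = 757: 90.0%.
- n = 726: 1 / (6 × √(2/726)) = 3.175; 3.175 − 1.960 = 1.215; Φ = 88.8%.

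The inflation slip therefore costs about 1.2 percentage points.

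**5. Power of the intention-to-treat analysis, 908 per arm.** SD √(2/n) = 6 × √(2/908) = 0.2816.
- No dilution (δ = 1 day): 1/0.2816 = 3.551; minus 1.960 = 1.591; Φ = 94.4%.
- Drop-outs gain nothing (δ = 0.8 × 1 + 0.2 × 0 = 0.8 day, SD still 6): 0.8/0.2816 = 2.841; minus 1.960 = 0.881; Φ ≈ 81%.

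**6. Mortality.** With 714 kept as the base, the total after 20% drop-out is 1,786, which is below 1,816. The base itself does not follow from the stated inputs by the standard formula: 28% in each group, margin 8%, one-sided 2.5% and 90% power give 10.507 × 2 × 0.28 × 0.72 / 0.08² = 661.9, so 662 per arm. Then 662/0.8 = 827.5, so 828 per arm and 1,656 in total. On either base, 1,816 is enough.

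**The case against.** **The primary analysis does not lose these patients.** This is the strongest objection, and it stands in part. The plan's drop-outs are not missing data. They are patients whom the intervention could not reach in time, and intention to treat keeps them in. A reader might infer from 726 that the primary analysis falls short of 90% power. The documents do not support that: the primary analysis has 908 per arm, and its power depends on how far the drop-outs dilute the effect, which the plan does not say. It could be above 90% (about 94%) or well below (about 81%). The objection does not rescue the arithmetic. The paragraph still names 757 as the number needed and 20% as the loss, and 908 does not reconcile the two.

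**Twenty per cent could be read relative to the patients who remain.** On that reading 151 extra patients on 757 is 20%. But 151 of 908 enrolled is 16.6%, and a drop-out rate is ordinarily a share of those enrolled. If the other meaning was intended, the text needs to say so.

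**The effect is small.** This stands. A loss of 1.2 points lies well within the uncertainty about the SD, and no endpoint or analysis changes.

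**Two further inferences go too far.** One is that 1,786 is the right mortality total. It is right only if 714 is, and the stated inputs give about 662 per arm. The other is that the slip compounds with the 0.0294 level in the section Interim analysis. The article gives that level only for the interim look, alongside the 8% margin, and does not say that the final comparison of duration uses it. That is a separate question and adds nothing to the size of this one.

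**Conclusion.** The error is real and follows from the plan's own figures. The 20% allowance was applied as × 1.2 where ÷ 0.8 is needed, in both calculations. For duration, 908 per arm leaves 726 patients against 757 stated as needed, and it covers 16.6% drop-out.

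The consequence is modest. Among patients who could receive a stopping advice, power at two-sided 5% is about 88.8% instead of 90%, given the 1-day difference that the plan implies but does not state. This is not evidence that the primary intention-to-treat analysis is underpowered. That analysis has between about 81% and 94% power, depending on an unstated dilution and with the SD held at 6 days. For mortality the slip has no practical effect, because 1,816 exceeds the requirement whether the base is 714 or 662.

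**What to change.** Keep 1,816 patients and correct the text:

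1. Say either that 908 per arm allows for 16.6% drop-out at 90% power, or that 20% drop-out leaves 726 per arm with about 89% power. State the 1-day difference and the two-sided level on which this rests, once the sponsor has confirmed them.
2. Add that these figures refer to patients who could receive a stopping advice, and that the intention-to-treat analysis keeps all 908 per arm, with power from about 81% (drop-outs gain nothing) to about 94% (no dilution).
3. For mortality, note that 1,714 has the same inflation error, that the total would be 1,786 if 714 is kept as the base, and that 1,816 still covers it.

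The cost is a few sentences and a slightly lower stated power. No further recruitment is asked for; the Abstract reports 1,600 of the 1,816 already randomised.
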